### Statistical analysis

Analysis will be performed as intention to treat. At baseline, the comparability of the intervention and control groups will be assessed. Quantitative variables will be described as the mean and standard deviation if they have a normal distribution, or median and range, as appropriate. Qualitative variables will be described as percentages and confidence intervals. Quantitative baseline characteristics will be compared using Student t test. Qualitative variables will use the Pearson chi squared test.

Multi-level multivariate survival analysis will include two effects (fixed and random). The fixed component of the adjusted model will include the group assignment and a dummy variable for baseline and 12-month measurements of the study variables, as well as interactions between relevant variables. All significant covariates in the bivariate analyses (p< 0.30) will be included in the model. This strategy will sufficiently reduce the probability of leaving relevant variables out of the model.

The primary response variable will be continued abstinence at 12 months after beginning smoking cessation (D-Day). We will use multiple techniques to deal with missing values in covariates that are candidates for inclusion in multi-level models. The ’ICE” programme of the STATA-10.1 package estimates missing values by conditional logistic regression, concatenating them with the variables that have complete values. As a convention, a combination of 10 different estimates will be used that includes the variability of these estimates. This will preclude a loss of power due to missing data. In addition, analysis of the models will be repeated to determine sensitivity, using only the subjects for whom complete data are available.

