#### Randomisation

The unit of randomisation will be the primary care centre, stratified according to urban/rural location and number of participating professionals to ensure comparability between the study groups, and then assigned 1:1 to the intervention or control group. Randomisation will use the Epidat 3.0 programme.

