### Sample size/power calculation

To calculate sample size for each primary care centre, the number of individuals in a simple randomized design was multiplied by the design effect. Accepting an alpha risk of 0.05 and a beta risk of 20% in a bilateral contrast, 222 subjects are required in each group to detect a difference of at least 5% (calculations based on EPIDAT v. 3.1). To calculate design effect, we estimated the intracluster correlation coefficient (ICC) in clinical trials randomized by primary care clusters, generally less than 0.05 [12], and as a cluster size. The average size is 20 with a design effect of 1.36. Assuming these values, the definitive sample size for the study was set at 604 subjects, randomised as described above.

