## Discussion

The development of the proposed smartphone app, and subsequent evaluation of its effectiveness in our population, has the potential to contribute a useful tool for the smoking cessation efforts of young adults, as well as providing information about the effectiveness of smoking cessation interventions in a population that has not been studied in our environment.

A limitation of the study is its open character. Both patients and health care professionals will know that they are involved in the intervention, which might create a bias. The analysis will be blind, with no identifiers available to the statistician that would indicate whether a subject was assigned to the intervention or control group. The study will use random clustering of primary care centres to avoid the risk of contamination by taking geography into account.

The randomization process is intended to result in a balanced distribution of sociodemographic and cultural characteristics between intervention and control groups, both for doctors and nurses and for participating patients. To avoid contamination between the intervention and control groups, the game and the app itself will only be made available to the intervention group. Multivariate analysis will be used to control for possible confounding factors.

Another limitation is the difficulty of recruiting young patients who want to stop smoking. The multicentre study design, with 22 participating primary care centres and a long (18-month) recruitment period, is intended to ensure an adequate participant pool.

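### Baseline characteristics of the arms are compared with patient-level t and chi-squared tests although centres are randomised, so ordinary between-centre variation may be reported as significant imbalance

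*Protocol article*

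**What the plan says.** On allocation, the Randomisation section states: "The unit of randomisation will be the primary care centre, stratified according to urban/rural location and number of participating professionals". Centres are stratified "and then assigned 1:1 to the intervention or control group".

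On clustering, the section Sample size/power calculation puts the intracluster correlation in primary care trials at generally below 0.05 and continues: "The average size is 20 with a design effect of 1.36".

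On baseline, the Statistical analysis section says that comparability of the two groups will be assessed and names the tests: "Quantitative baseline characteristics will be compared using Student t test. Qualitative variables will use the Pearson chi squared test". It mentions no adjustment for centre here. A random component appears only in the next paragraph, for the multilevel survival analysis of the outcome.

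The Discussion states the expectation that the comparison bears on: "The randomization process is intended to result in a balanced distribution of sociodemographic and cultural characteristics between intervention and control groups".

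**The concern.** The Student t test and the Pearson chi-squared test take their variance from independent patients. When whole centres are allocated, the chance difference between arms also contains the variation between centres, which these tests leave out. Any positive within-centre correlation therefore makes them reject too often, even when allocation of centres has produced only the differences expected by chance. The article allows for this correlation in the sample size but not in this comparison.

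The comparison is informative in this trial. Centres are randomised once they agree to take part (Selection of participating primary care centres). Their own doctors or nurses then invite the patients (Intervention) and cannot be masked (Blinding). The Discussion accepts that this openness might introduce bias. Recruitment could thus differ between arms after allocation, and the baseline table is a natural place to see it. A test that also responds to ordinary differences between centres cannot tell the two apart.

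**Working it through.** **Inputs.** From Sample size/power calculation: 222 per group before inflation, average cluster size 20, design effect (DE) 1.36, total 604, ICC generally below 0.05, two-sided alpha 0.05. From the Discussion: 22 centres. The article gives no significance level for the baseline tests, so 0.05 is borrowed from the sample size section.

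**The plan's own figure.** 222 × 1.36 = 301.92, rounded up to 302 per arm; 2 × 302 = 604. This reproduces the stated total.

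**ICC implied by the plan.** DE = 1 + (m − 1) × ICC, so ICC = (1.36 − 1)/(20 − 1) = 0.019.

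**Cluster size.** The plan states m = 20, but 604 patients over 22 centres gives m = 604/22 = 27.5. Both are shown.

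**Formula.** A test that ignores clustering understates the variance of the arm difference by the factor DE. Its actual two-sided error at nominal 5% is 2 × [1 − Φ(1.96/√DE)]. For DE = 1.36: 1.96/1.166 = 1.68, which gives 9.3%.

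| ICC | DE, m = 20 | Error rate | DE, m = 27.5 | Error rate |
|---|---|---|---|---|
| 0.005 | 1.10 | 6.1% | 1.13 | 6.6% |
| 0.01 | 1.19 | 7.2% | 1.26 | 8.1% |
| 0.019 (implied) | 1.36 | 9.3% | 1.50 | 11.0% |
| 0.03 | 1.57 | 11.8% | 1.79 | 14.3% |
| 0.05 (cited upper figure) | 1.95 | 16.0% | 2.32 | 19.8% |
| 0.10 (beyond the cited range) | 2.90 | 25.0% | 3.65 | 30.5% |

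**Check by simulation.** With 10,000 null trials per setting, equal centre sizes and no stratification, the patient-level t test rejected as follows:

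- 15 centres of 20 per arm: 8.9% at ICC 0.019 and 15.9% at ICC 0.05.
- 11 centres of 27 per arm: 10.7% at ICC 0.019 and 19.6% at ICC 0.05.

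A separate simulation of 6,000 trials per setting, with a binary variable of prevalence 0.30, 22 centres and 604 patients, gave 10.4% and 19.9% for the Pearson chi-squared test at the same two ICCs. A t test on centre means in the first set of simulations stayed between 4.7% and 5.1%, so the nominal rate is recovered when the centre is the unit of analysis.

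**The case against.** The strongest reply is that little depends on these tests. The outcome is analysed with a multilevel model, and the article attaches no decision rule to a baseline p-value. That stands, and it limits the weight of the point.

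The size is also conditional. The planning ICC belongs to the sample size calculation, and nothing is said about the ICC of age, sex, education or cigarettes per day. At an ICC of 0.01 or below the inflation is modest. Stratifying by location and number of professionals could reduce it somewhat, while unequal centre sizes would raise it. This stands too: no single multiple of 5% can be stated as fact. The 20% end needs both the cited upper ICC and 27.5 patients per centre instead of the stated 20.

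Some stronger readings are tempting but not supported:

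- A reader might infer that these tests decide which confounders are adjusted for. The article selects covariates from bivariate analyses at p < 0.30 but does not say that these are the comparisons between arms; they could equally relate covariates to outcome.
- A reader might infer that the treatment comparison is inflated. Nothing in the text supports that.
- A reader might compound the error over roughly 15 baseline variables: 1 − 0.95^15 = 54% with valid tests against 1 − 0.89^15 = 83% at an 11% rate. This assumes independence, which is implausible for variables such as education, employment and social class, and most of the total comes from multiplicity alone.
- A reader might infer that the confidence intervals for baseline percentages are too narrow. The article does not say how they are computed.

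What survives is that the named tests do not match the design, and that no other part of the article corrects this.

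**Conclusion.** The point holds and is minor. The tests named for baseline comparability use the wrong variance for a trial that allocates centres, and this contradicts the plan's own assumption of within-centre correlation. Against a nominal 5%, the false-positive rate is about 9% to 11% at the ICC implied by the design effect, and 16% to 20% at the cited upper value. These figures assume that baseline variables cluster like the planning ICC, that centres are of equal size, that stratification removes none of the between-centre variation, and that the tests are read at 5%. The direction holds for any positive ICC that stratification does not absorb; the size is not fixed by the article. The consequence is a potentially misleading baseline table, not an error in the primary analysis.

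**What to change.** In the Statistical analysis section, replace the two sentences on baseline tests in one of two ways:

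- Take any test between arms from centre-level summaries (a t test on centre means or proportions, with 22 − 2 = 20 degrees of freedom before allowing for strata), or from a mixed model with a random centre effect.
- Drop the tests and describe baseline by arm at both centre and patient level.

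If between-arm intervals are reported, compute them with a cluster-adjusted variance.

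The cost is a few words and minor programming, with no new data. Intervals become wider by the square root of the design effect: √1.36 = 1.17, about 17%, and √2.32 = 1.52, about 50%, at the upper end.

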### Measures

During the recruitment visit, sociodemographic and anthropometric variables will be recorded: age, sex, educational level, employment, weight, height and blood pressure. Social class will be categorized according to the British Registrar General’s Social Classification [11]. Variables related to tobacco consumption also will be recorded: number of cigarettes smoked per day, start age, number of previous cessation attempts, longest period of cessation, and presence of other smokers in the family. The degree of nicotine dependence will be measured by the Fageström test. Motivation to stop smoking will be assessed by the Richmond test.

During follow-up visits, weight, height, and blood pressure will again be measured. Participants will be asked about their tobacco use and presence of withdrawal symptoms (vehement desire to smoke, anxiety, tension, nervousness, frustration, impatience, difficulty in concentrating, hunger, drowsiness or difficulty in sleeping, nightmares, headache, irritability/depression), and CO in exhaled breath will be measured by carboximetry.

At each visit, the professional who provided smoking cessation information (doctor or nurse) and any treatment provided will be recorded. We will also record the smoking cessation date (D-day) and the date of the end of follow-up, either 12 months after D-day or date lost to follow-up (D2). We will then calculate the length of the follow-up period. (With these variables the length of survival can be calculated: time interval between start date of smoking cessation and relapse or end of follow-up).

Tobacco abstinence will be confirmed by the level of carbon monoxide (CO), set as 10 parts per million or less, measured by carboximetry readings taken by trained personnel.

The follow-up period will have the following end-points: (1) 12 months after D-Day; (2) participant decides not to continue in the study, informs study personnel, and abandons participation; (2) participant is lost to follow-up, provides no more information, and will be considered relapsed as of that time point.

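### The fixed part of the adjusted survival model carries a baseline/12-month term that does not suit a time-to-relapse outcome, and one reading of it adjusts for post-randomisation variables.

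*Protocol article*

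**What the plan says.** All references are to the Protocol article.

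- **Model (Statistical analysis).** The between-group model is a multi-level survival model with fixed and random effects. Its fixed part holds group assignment and "a dummy variable for baseline and 12-month measurements of the study variables, as well as interactions between relevant variables".
- **Covariate selection (same section).** "All significant covariates in the bivariate analyses (p< 0.30) will be included in the model". The rule does not say that candidates must be baseline variables.
- **Outcome (Statistical analysis; Measures).** The primary response is continued abstinence 12 months after D-Day. Survival time is the "time interval between start date of smoking cessation and relapse or end of follow-up".
- **What is measured after randomisation (Measures).** "During follow-up visits, weight, height, and blood pressure will again be measured". In addition, "Participants will be asked about their tobacco use and presence of withdrawal symptoms", and exhaled CO is read. CO at or below 10 ppm is what confirms abstinence.
- **Losses (Measures).** A participant who is lost gives no further data and counts as relapsed from that moment.
- **Aims of the analysis (Statistical analysis; Discussion).** The analysis is by intention to treat, and multivariate adjustment is there to deal with confounding.

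**The concern.** In a randomised trial, the group coefficient estimates the effect of assignment when the model adjusts only for things fixed before assignment. A covariate measured at 12 months can be a step on the path from the app to abstinence (withdrawal symptoms), a consequence of abstinence (weight, blood pressure), or part of the outcome itself (tobacco use, CO). Once such a variable is in the model, the coefficient no longer answers the intention-to-treat question. Nor does the adjustment serve its declared purpose, because a value that arises after allocation cannot confound the allocated comparison.

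A survival model adds a timing problem: a value taken at month 12 cannot explain a relapse in month 2.

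This is the only between-group outcome model that the article describes. The problem lies in wording that is present, so it is not a matter of detail left to a fuller document.

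**Working it through.** The plan gives no figure for this point to reproduce. The check is a reading of the sentence in both possible senses, followed by an illustration of size.

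**Reading A: the 12-month values are covariates.**

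1. The article does not list its study variables. Those it re-measures in follow-up are weight, height, blood pressure, tobacco use, withdrawal symptoms and CO. All except height can respond to the app or to abstinence.
2. Time runs from D-Day to relapse, or to month 12 at the latest. For every participant who relapses before month 12, the covariate is dated after the event it is meant to explain.
3. Lost participants count as events but have no 12-month values. The planned multiple imputation would have to supply them. The planned complete-data sensitivity analysis would drop these participants, and so remove events that the loss-equals-relapse rule had counted.

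**Reading B: a single indicator of measurement occasion, baseline versus 12 months.**

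1. Such a term belongs in a repeated-measures model with two records per person.
2. Here each participant contributes one time to relapse, starting at D-Day. All are smokers of at least 10 cigarettes a day at entry (Patient inclusion criteria), so there is no baseline value of the outcome to contrast with month 12. The indicator has nothing to estimate.

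**The selection rule.** A follow-up variable that changes with relapse will tend to pass a bivariate screen at p < 0.30. As worded, the rule could admit such variables even if the baseline/12-month term were removed.

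**Illustration of size under reading A.** Every parameter below except the total of 604 is an assumption. None is an estimate for this trial.

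*Simulation 1: 12-month variables are consequences of relapse.* Cox model, 604 participants, 30 clusters, about 5% abstinent in the control group, 300 replicates. The fitted model had no random centre effect.

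| True HR | Model | Mean HR | Tests significant |
|---|---|---|---|
| 0.75 | baseline covariate only | 0.78 | 80% |
| 0.75 | + 12-month weight, withdrawal | 0.80 | 69% |
| 0.75 | + 12-month CO | 0.82 | 61% |
| 0.80 | baseline covariate only | 0.82 | 60% |
| 0.80 | + 12-month weight, withdrawal | 0.84 | 53% |
| 0.80 | + 12-month CO | 0.86 | 45% |

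The loss in significant tests is 80 − 69 = 11 and 80 − 61 = 19 points at HR 0.75, and 60 − 53 = 7 and 60 − 45 = 15 points at HR 0.80. At a true HR of 1.0 all models gave about 1.00, with 9% to 10% of tests significant. Because clustering was ignored in the fit, the percentages are useful only for comparing models with each other.

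*Simulation 2: how direction depends on structure.* Logistic model, 604/2 = 302 per arm, no clustering. A follow-up score has SD 1, and logit P(abstinent) = −3.3 − 1.0 × score + b × arm.

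| Shift of score in app arm | b | Group log OR without score | Group log OR with score |
|---|---|---|---|
| −0.4 | 0.35 | 0.72 | 0.37 |
| 0 | 0.70 | 0.66 | 0.72 |
| +0.4 | 0.90 | 0.47 | 0.92 |

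In the first row adjustment roughly halves the coefficient; in the other two it raises it. The adjusted column largely gives back the assumed b, so the table shows that direction depends on structure and says nothing about size in this trial.

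**The case against.** The strongest objection is that the phrase uses the singular: one dummy variable cannot carry the values of weight, blood pressure, CO and symptoms. With the mention of interactions, it resembles ordinary repeated-measures wording with a group-by-time term, which conditions on no 12-month value. The Discussion's stated aim of controlling confounding also argues against any intention to adjust for mediators. This stands as far as it goes: reading A cannot be treated as certain. It does not rescue the sentence, because an occasion indicator has no role in a one-event survival model.

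A second objection is that no section names CO or 12-month tobacco use as a covariate. That is right. The list of candidates is inferred from what Measures says is recorded in follow-up.

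Third, leaving the interactions unnamed is normal in a condensed article. That is accepted, and it is not part of the defect.

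A reader might infer three stronger things that the documents do not support:

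- **That the model removes the app's effect.** The wording does not settle that 12-month values enter at all, and in Simulation 1 the effect shrank but did not vanish.
- **That the bias always runs towards no effect.** Simulation 2 shows both directions.
- **That 12-month CO or tobacco use would separate the outcome perfectly.** The outcome is continued abstinence, so someone who relapsed and quit again can read 10 ppm or less at month 12, and lost participants have no reading.

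**Conclusion.** The point holds in this form: the fixed part of the adjusted model is specified ambiguously, and it is unsuitable for time to relapse on either reading. If 12-month values are covariates, the group effect is conditioned on post-randomisation variables and can be attenuated or otherwise distorted, against the intention-to-treat aim. If the term marks the measurement occasion, it is meaningless in this model. The selection rule leaves the same door open.

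The size and direction of any distortion depend on which variables enter and how they relate to the app and to relapse, and the article fixes neither. The simulated figures show only that the distortion need not be negligible. The conclusion itself rests on the wording of Statistical analysis and Measures, and on no simulation.

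**What to change.** In the Statistical analysis section:

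1. Delete the baseline/12-month term from the primary model.
2. State that this model contains only group, the randomisation strata (urban/rural location and number of participating professionals, from Randomisation), prespecified baseline covariates and a random centre effect.
3. Limit the p < 0.30 rule to baseline variables, or drop it.
4. Keep interactions out of the primary effect model and test any of interest in a separate analysis.
5. Analyse follow-up weight, blood pressure and withdrawal symptoms as separate outcomes.

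The cost is a rewording of the analysis paragraph. Data collection, sample size and conduct are unchanged.

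### The adjusted model picks its covariates by a p<0.30 screen on the trial's own data, so neither the stratification factors nor the main baseline predictors are sure to be in it

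*Protocol article*

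**What the plan says.** All references are to the protocol article.

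- **Statistical analysis, entry rule:** "All significant covariates in the bivariate analyses (p< 0.30) will be included in the model". The stated justification is that "This strategy will sufficiently reduce the probability of leaving relevant variables out of the model".
- **Statistical analysis, fixed terms:** "The fixed component of the adjusted model will include the group assignment and a dummy variable for baseline and 12-month measurements of the study variables", together with interactions that are not named. The model is multi-level, with fixed and random effects.
- **Statistical analysis, baseline tests:** the only bivariate tests described are comparisons of the two groups at baseline. "Quantitative baseline characteristics will be compared using Student t test", and qualitative variables use the Pearson chi-squared test.
- **Randomisation:** centres are "stratified according to urban/rural location and number of participating professionals to ensure comparability between the study groups", then "assigned 1:1 to the intervention or control group".
- **Measures:** the baseline variables are "age, sex, educational level, employment, weight, height and blood pressure", social class, "number of cigarettes smoked per day, start age, number of previous cessation attempts, longest period of cessation, and presence of other smokers in the family", and the Fagerström and Richmond scores.
- **Selection of participating primary care centres, Blinding, Intervention:** centres are allocated and their staff then briefed, staff cannot be masked, and the same doctors and nurses invite the patients.
- **Discussion:** 22 centres take part, and multivariate analysis is the stated means of controlling confounding.

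**The concern.** This is a stated selection method, not a detail left for later. Whether a covariate is adjusted for depends on its p-value in the data being analysed. Four things follow.

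1. The design used two factors to make the groups comparable, but nothing carries them into the analysis. Both vary only between centres, and there are 22 centres, so evidence on their association with outcome is thin.
2. Patients are recruited by unmasked staff who already know their centre's arm. Randomising centres does not protect against differences in who is then enrolled. Adjustment for dependence, motivation and consumption is the natural safeguard, and here it depends on a test. A modest imbalance in a prognostic variable can matter without being flagged.
3. The screen is not fully defined. Screening against outcome selects variables that look prognostic in this sample. Screening against group, the only kind of bivariate test that the section describes, selects chance imbalances. The two can give different models.
4. The adjusted estimate depends on a covariate set that nobody can name in advance. If it is a hazard or odds ratio, the quantity estimated itself shifts with that set. Blinding the analyst limits deliberate choice but does not fix the model.

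**Working it through.** **The plan's own figure.** 222 per group × 2 × design effect 1.36 = 603.84, rounded up to 604. This reproduces, so N = 604 is used below.

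**Candidates.** From Measures: 7 sociodemographic and anthropometric variables plus social class = 8; 5 tobacco variables plus Fagerström and Richmond = 7. Total 15.

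**Chance entries.** A variable with no association passes with probability 0.30. If all 15 were null and independent, 15 × 0.30 = 4.5 would be expected to enter, and P(at least one) = 1 − 0.70^15 = 99.5%.

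**Chance that a real factor fails the screen.** Take a two-sided two-proportion test at 0.30 (z = 1.036) against outcome, with a factor split 50/50.

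- Per-level size: m = 604/(2 × DE), where DE is the design effect.
- Standard errors: se0 = √[2p̄(1−p̄)/m] and se1 = √[(p1(1−p1)+p2(1−p2))/m].
- P(fail) = Φ[(1.036·se0 − d)/se1] − Φ[(−1.036·se0 − d)/se1], with d = p2 − p1.
- DE = 1.36 is the protocol's value. DE = 1 + 19 × 0.05 = 1.95 uses its average cluster size of 20 and the upper ICC that it quotes, 0.05. DE = 1 represents a patient-level factor.
- Abstinence rates are assumptions. 5.8% vs 8.1% and 4% vs 9% are borrowed from the Background, where they are trial-arm results and not effects of a covariate. 5% vs 8% is a further illustration.

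Worked case, 5.8% vs 8.1% at DE 1.36: m = 222.1, se0 = 0.02413, se1 = 0.02411, d = 0.023. P(fail) = Φ(0.084) − Φ(−1.991) = 0.533 − 0.023 = 0.51.

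| Abstinence by level | DE 1 | DE 1.36 | DE 1.95 |
|---|---|---|---|
| 5.8% vs 8.1% | 45% | 51% | 56% |
| 5% vs 8% | 32% | 39% | 47% |
| 4% vs 9% | 7% | 13% | 22% |

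A modest centre-level factor therefore fails 39% to 56% of the time and a modest patient-level factor 32% to 45%. A strong one usually passes.

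**If the screen ignores clustering.** The threshold then uses the DE 1 standard error, while the estimate varies with the clustered one. For 5.8% vs 8.1% the threshold is 1.036 × 0.02069 = 0.0214. At DE 1.36, P(fail) = Φ[(0.0214 − 0.023)/0.02411] − Φ[(−0.0214 − 0.023)/0.02411] ≈ 0.47 − 0.03 = 44%. The factor is dropped less often, but still often.

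**Type I error.** 6,000 trials were simulated with 604 individuals, 15 covariates (three prognostic, log odds ratio 0.3 per SD), about 6–7% abstinence and a linear model on the binary outcome. True predictors passed the screen 77% of the time, and 3.6 of 12 null variables entered. Rejection at nominal 5% was 4.9% (screened on outcome), 4.5% (screened on group), 4.5% (pre-specified) and 4.7% (unadjusted). Simulation error is √(0.05 × 0.95/6000) ≈ 0.3 percentage points, so none of these shows inflation. The simulation had no clustering and no survival times.

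**The case against.** - **The validity harm is not shown.** A reader might infer that screening invalidates the confidence interval or inflates type I error. Nothing in the article shows this, and the simulation above does not either. This objection stands.
- **The baseline tests are a separate matter.** A reader might add that the t and chi-squared comparisons ignore clustering and so have an inflated 5% error rate. The article ties no decision to a 5% baseline test, and if the screen is against outcome those tests select nothing. They do not strengthen the point.
- **The lost precision may be small.** With 22 centres (20 degrees of freedom), missing p<0.30 means |t| < 1.064. The factor then explains less than 1.064²/(1.064² + 20) = 5.4% of between-centre variance in that dataset. Omitting a prognostic stratification factor normally makes the analysis conservative, not biased. This stands, so precision is a minor part of the case.
- **Chance entries cost little.** The figure of 4.5 assumes that every candidate is null, and a few extra patient-level covariates do little harm with 604 participants. This stands.
- **The text gives an inclusion rule only.** Exclusion of everything else is implied by the stated justification, not written outright, and an article may leave its covariate list to a fuller document. This stands in part: the article cannot be read as excluding the stratification factors. But a p<0.30 rule is what it states, and it exempts nothing from that rule.

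**Conclusion.** The point holds, as a change worth making rather than a fatal flaw. The article fixes a data-driven way of choosing covariates, leaves the direction of the screen undefined, and guarantees a place neither to the stratification factors nor to any named baseline predictor. Under the illustrative modest associations, a 50/50 centre-level factor fails a cluster-aware screen about 39% to 56% of the time. With the stronger 4% vs 9% the figure is 13% to 22%. All these figures rest on assumed abstinence rates, a normal approximation and a screen against outcome.

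The consequences are an estimate whose covariate set is not fixed in advance, an analysis that may not reflect the stratified design, some possible loss of precision, and adjustment for recruitment imbalance that cannot be relied on. The documents do not support a claim of inflated type I error.

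**What to change.** In Statistical analysis, replace the p<0.30 rule for the primary model with a fixed list:

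- group;
- urban/rural location and number of participating professionals;
- a short list of named baseline predictors, for example Fagerström score, Richmond score and cigarettes per day;
- the random centre effect already planned.

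The choice of predictors is for the trial team, provided it is made before outcome data are seen. Any screened model should be kept as a sensitivity analysis only, stating whether its screen is against outcome or against group.

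Only wording changes. The patient variables are already collected, the centre factors are known at randomisation, and the sample size is unaffected. The downside is a few model degrees of freedom, including two centre-level terms estimated from 22 centres.
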